## Discussion

Active transportation with traditional bicycles has shown potential to increase PA levels [7, 8] and reduce climate gas emissions related to car use [21], thereby promoting public health and environmental sustainability. E-bikes are becoming increasingly popular, yet current knowledge is sparse regarding influence of e-biking on travel behavior and total levels of PA [34]. The feasibility of e-bikes as mode of transport among parents of toddlers should be explored, considering the impact of parental PA and transportation habits on their children’s future habits. Also, there is a call for increased understanding whether voluntary cycling with e-bikes could improve health. In addition to e-bikes, longtail bikes could possibly contribute positively to both increased bicycling in everyday life, as well as a shift from cars to bikes, as they may meet needs related to transportation of children and goods not sufficiently accomplished by traditional bikes or e-bikes. However, this likely potential of longtail bikes has not previously been scientifically explored. Therefore, the project “From cars to bikes” aims to assess the feasibility and effect of an intervention providing participants free access to an e-bike (including a trailer), a longtail bike, and a traditional bike (including a trailer) for an extended period of in total nine months. Study objectives of the present project are in accordance with aims presented in international and national strategic documents, such as the Paris Agreement [23], the Norwegian National Transportation plan 2018–2029 [75], the latest Norwegian White Paper on public health, “Mastering and opportunities” [76], and both national [77] and global [1] recommendations for PA. Hence, “From cars to bikes” will add new knowledge to topical issues related to public health and environmental sustainability in a target group of utmost relevance, i.e. parents of toddlers.

The strengths of the present study are firstly that the intervention is being conducted in a natural setting with accessibility to different bicycle types representing the intervention arms, and no instructions in terms of bicycling amount. Thus, the effect of accessibility on voluntary cycling (distance, time and pace) and potential health effects can be examined - in other words, both effectiveness and efficacy [78]. As discussed herein, we need increased knowledge regarding potential health effects (efficacy) of using e-bikes and longtail bikes for transportation. Still yet, public health and environmental gains will be attenuated if it turns out that bicycling for transportation does not represent a feasible mode of transport for parents with children attending kindergarten, and “compliance” (bicycling) is low (effectiveness), meaning that both effectiveness and efficacy are relevant aspects. In this regard, inclusion of semi-structured qualitative interviews will enrich the study, as it allows for an exploration of participants’ experiences and pros and cons with bicycling for transportation, when using different bicycle types. An additional advantage is that the cross-over design (within design) removes variability between subjects and thus increases power, compared with a parallel group design (between design). Also, as opposed to a between design, comparability of subjects within conditions is enabled. Further, the use of a reference method for assessing body composition (DXA), and objective measures of total levels of MVPA (SWA) and amount of bicycling (cycle computer and smartphone-app), are study strengths.

Nonetheless, there are some study limitations. The intervention is quite straightforward, addressing accessibility as one main behavioral determinant, yet reality is more complex. If other determinants are equally or even more important than accessibility, we may not achieve behavior change due to exclusion of these other determinants. Moreover, if effectiveness comes out low, i.e. parents are not bicycling, we will not obtain enough data to draw any conclusions regarding potential health effects from bicycling for transportation. Also, sample size and study power are shortcomings; we expect to detect significant differences in the physiological parameters between the control and intervention group, yet not between the three intervention arms. Still, relevant knowledge regarding total amount of bicycling (main outcome) and PA, as well as travel habits and motivation, is likely to be acquired across the bicycle types. It should be mentioned though, that period effects and carry-over effects could influence these latter aspects, due to the lack of wash-out periods between the intervention arms. Besides, the cross-over design requires a longer study period than a parallel group design, which may increase the drop-out risk. And, because we are recruiting a convenience sample, self-selection and homogeneity is likely to impair generalizability.

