### Study sample

A convenience sample consisting of 36 parents of toddlers residing in Kristiansand municipality, Southern Norway, will be recruited. Main outcome will be total amount of bicycling (distance and time). Due to few previous studies in e-bikes and none in longtail bikes targeting total amount of bicycling, power calculations are challenging to perform. However, based on a standard deviation (SD) of 60 min/week [48], a power of 0.80 and a significance level of 5%, we will be able to detect an increase in cycling time from 15 min (based on inclusion criteria) to 75 min a week (i.e. half of weekly PA recommendations) with 16 subjects in the intervention group and 16 subjects in the control group. Yet, to account for 10% drop-out, and to utilize the bikes optimally according to the study design (see Table 1), we will include 18 subjects in both groups (intervention and control). Inclusion criteria are: (i) being able to understand and read Norwegian, (ii) having one child born in year 2013, 2014 or 2015, attending kindergarten, (iii) being responsible for bringing/picking up the child in the kindergarten ≥5 times per week/at least half of the times, (iv) residing 2–10 km from the workplace, (v) residing <3 km from the kindergarten and the grocery shop, (vi) having car-access (vii) possessing a smartphone requiring personal pin code or comparable safety solution for usage, (viii) being between 167 and 190 cm tall (due to the size of accessible bikes), and (ix) have the opportunity to store the bikes indoors. Exclusion criteria are: (i) being physically active, i.e. meeting the PA recommendations [1, 45], (ii) having bicycled more than once weekly during the last twelve months to the workplace, kindergarten or the grocery shop, and (iii) suffering from severe cardiovascular diseases or upper respiratory tract diseases.

**Table 1 Tab1:** Possible combination of intervention arms

Month 1–3	Month 4–6	Month 7–9	
E-bike	Longtail	Traditional	*n* = 3
E-bike	Traditional	Longtail	*n* = 3
Longtail	E-bike	Traditional	*n* = 3
Longtail	Traditional	E-bike	*n* = 3
Traditional bike	E-bike	Longtail	*n* = 3
Traditional bike	Longtail	E-bike	*n* = 3

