#### Bicycle use and total physical activity level

Total amount of bicycling (i.e. cycling distance, time and pace) will be measured with a cycle computer and an appropriate smartphone application, the latter being developed at UiA in cooperation with Department of Information and Communication Technology. The app shall include a diary-function, enabling registration of bicycle type (el/longtail/traditional) and trip purpose. Total time of MVPA will be measured for seven consecutive days at study start and connected to each intervention arm (at 3, 6 and 9 months), using the monitor SenseWear Armband Mini (SWA; BodyMedia, Pittsburgh, Pennsylvania, USA). Data will be downloaded using the software SenseWear Professional V.8.1 (BodyMedia, Pittsburgh, Pennsylvania, USA), with a valid day defined as at least 80% (19.2 h) wearing time. To be included in the analyses, participants need to provide a minimum of four valid days, comprising at least one weekend day [65, 66]. The cut-off defining MVPA will be 3 METs [67]. In addition, seasonal variations in bicycling amount will be explored, and weather data (temperature, rainfall, snow, etc.) will be collected.

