### Quantitative and qualitative data analyses

The statistical analyses for the quantitative data will be performed using the statistical software package IBM SPSS Statistics version 24.0 (IBM Corp., Somers, New York, USA). A two-sided *p*-value of <0.05 will be considered statistically significant. Descriptive analyses will be conducted and continuous variables will be presented as means and standard deviations (SD), categorical variables as proportions. Moreover, regression analyses will be performed according to Twisk and Proper [73], using data from the post-measures adjusting for baseline measures, to assess differences between (1) the control group and the intervention group (between design) for all outcome variables, and (2) within the intervention group when comparing the three different arms regarding total amount of bicycling and PA, transportation habits, and self-reported health and HRQoL.

A qualitative content analysis will be conducted from a phenomenologic-hermeneutic perspective [74]. Recordings of the qualitative interviews will be transcribed verbatim and read repeatedly to grasp the meaning of the data as a whole. Data will then be imported into the software analysis program NVivo 11 for further analysis. The next step will be to separate the text into meaning units; i.e. the words, sentences or paragraphs containing aspects related to each other through their content and context. Following this, the meaning units will be classified into subcategories, by pooling data with similar characteristics together in a category defined by its content. Finally, the subcategories will be combined and categorized into main categories.

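### The stated model for comparing the three bikes adjusts only for baseline; a period term should be added, with first-order carry-over as one sensitivity analysis

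*Protocol article*

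**What the plan says.** - **Design (Study sample, Table 1, headed "Possible combination of intervention arms").** All six orders of e-bike, longtail and traditional bike are listed, with three participants in each. That gives 18 participants and 54 participant-periods of three months.
- **Analysis (Quantitative and qualitative data analyses).** Post-measures are regressed with adjustment for baseline. The same approach serves the comparison with control and the comparison "within the intervention group when comparing the three different arms regarding total amount of bicycling and PA". Baseline is the only adjustment named.
- **Limitation (Discussion).** For bicycling amount (the main outcome), physical activity, travel habits and motivation across bike types, the article concedes that "period effects and carry-over effects could influence these latter aspects, due to the lack of wash-out periods between the intervention arms".
- **Season (Bicycle use and total physical activity level).** Weather data will be collected and "seasonal variations in bicycling amount will be explored". The Objectives list this among the other study objectives. It is not described as an adjustment of the bike comparison.

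**The concern.** Each participant's nine months fall into three quarters of a year. If participants move through the periods together, as the month columns of Table 1 suggest, period largely coincides with season, and season plausibly matters for cycling in Norway. A baseline measured once before the first bike is the same for all three of a participant's periods. It therefore cannot absorb a period effect, nor anything left over from the previous bike.

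At stake is the comparison between bikes. The article presents reduced between-subject variability and greater power as advantages of the cross-over, and an unmodelled period effect gives part of that power back. An unmodelled difference in carry-over could shift the contrasts themselves, and the article describes no analysis that would show whether it had.

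**Working it through.** **1. The plan's own figure.** Inputs from Study sample: SD 60 min/week; "an increase in cycling time from 15 min (based on inclusion criteria) to 75 min a week", so a difference of 60; power 0.80; 5% level, two-sided by the analysis section. Normal approximation: n = 2 × (1.96 + 0.842)² × 60² / 60² = 15.7, so 16 per group. Allowing for 10% drop-out, 16 / 0.9 = 17.8, so 18. The stated numbers reproduce. They concern intervention versus control and do not depend on what follows.

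**2. Balance of Table 1.** Each bike appears in each period in 2 of 6 sequences (6 participants). Each ordered pair of bikes also appears in 2 of 6 sequences (6 participants). A least-squares model with 18 participant effects, bike (2), period (2) and first-order carry-over (2) has rank 24 of 24 parameters, leaving 54 − 24 = 30 residual degrees of freedom. Without carry-over there are 32, and without period 34. Both effects are estimable.

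**3. Assumptions not in the article.** Within-person correlation ρ of 0.3, 0.5 or 0.7; a middle-period dip of 40 min/week; participant effects in the model. The article does not say how repeated measurements are handled, but participant effects match its claim that the cross-over removes between-subject variability.

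**4. Omitting period, complete data.** Each bike has 6 of its 18 observations in every period, so a period shift moves all three bike means equally and every bike contrast has zero bias.

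The residual does change. Period effects (0, −40, 0) deviate from their mean by 13.3, −26.7 and 13.3, with sum of squares 1,066.7. Over 18 participants this is 19,200, which adds 19,200 / 34 = 565 to the residual mean square. The within-person variance is 3,600 × (1 − ρ), and the variance of a bike contrast is 2/18 = 0.111 times the residual variance.

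| ρ | Within-person variance | SE, period in model | SE, period omitted |
|---|---|---|---|
| 0.3 | 2,520 | √(2,520/9) = 16.7 | √(3,085/9) = 18.5 |
| 0.5 | 1,800 | √(1,800/9) = 14.1 | √(2,365/9) = 16.2 |
| 0.7 | 1,080 | √(1,080/9) = 11.0 | √(1,645/9) = 13.5 |

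In simulation, the true sampling SD of the contrast stays at the smaller value whether or not period is modelled. Only the reported SE is inflated. Simulated power for an assumed 40 min/week bike difference falls from 65 / 78 / 94% to 56 / 69 / 86% across the three correlations.

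**5. Omitting period, with drop-out.** Suppose two participants leave after period 1, both in an order with the e-bike second, then the longtail. Among the 16 who continue, 4 e-bike observations and 6 longtail observations fall in the dip. The e-bike mean shifts by −40 × 4/16 = −10 and the longtail mean by −40 × 6/16 = −15, so the contrast is biased by 5 min/week. That is the worst case. Averaged over all 153 pairs of leavers, the absolute bias is 2.5 × 132/153 = 2.2 min/week. (A pair gives 2.5 min/week times the difference between its counts of leavers with each bike second. These differences sum to 15×2 + 15×2 + 36×1 + 36×1 = 132.)

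**6. Omitting carry-over.** No bike follows itself, and each bike follows each other bike in 6 of that bike's 18 observations. With carry-over λ from each bike, the e-bike mean shifts by (λ_L + λ_T)/3 and the longtail mean by (λ_E + λ_T)/3. The bias in e-bike minus longtail is therefore (λ_L − λ_E)/3. Equal carry-over gives zero bias. If one bike leaves 30 min/week and the others none (an assumed figure), its contrasts shift by 10 min/week.

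**7. Cost of a carry-over term.** The variance of a bike contrast rises from 0.111 to 0.139 times the within-person variance, a ratio of 1.25, and √1.25 = 1.118, so the SE is about 12% wider. The carry-over difference detectable with 80% power is 73 / 61 / 48 min/week for ρ of 0.3 / 0.5 / 0.7.

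**The case against.** The strongest reply is that a journal article condenses its plan. One sentence pointing to a cited methods source is not a full specification, and silence on extra terms may mean only that they are written elsewhere. This stands in part: one can say that the article names neither term, not that no analysis will contain them. But the article does state an adjustment for this comparison, names baseline alone, and treats the two effects it concedes only as limitations.

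Second, the threats are disclosed, and random order with balanced sequences already protects the contrasts from period effects when data are complete. That is correct, and it limits the period point mainly to precision.

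A reader might go further in four ways that the documents do not support:

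- *Season distorts the bike contrasts.* With complete data it does not. It inflates the reported SE, so inference is conservative.
- *Carry-over must bias the result, usually towards no difference.* Bias needs unequal carry-over, and nothing in the article fixes its direction. If the bike that is cycled more also leaves more habit behind, the contrast shrinks; the opposite pattern exaggerates it.
- *The sequences were chosen in order to estimate these effects.* The article does not say so. Its reasons for 18 per group are drop-out and good use of the bikes.
- *A carry-over model would settle the matter.* At correlations of 0.5 or below, the detectable carry-over difference exceeds the 60 min/week effect on which the trial is sized.

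**Conclusion.** The point holds as a worthwhile improvement to a stated model, not as an error that invalidates the trial. Period is the main part: without it, the reported SE of a bike contrast is about 16 rather than 14 min/week at a correlation of 0.5, and power for a 40 min/week difference is about 69% rather than 78%. Drop-out adds a modest possible bias, typically about 2 and at worst 5 min/week when two participants leave after period 1. Carry-over is the lesser part: its bias is one third of any difference between bikes, of unknown sign, and 18 participants can estimate it only imprecisely.

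Only the SD of 60 min/week comes from the article. The correlations, the 40 min/week dip, the 40 min/week bike difference and the 30 min/week carry-over are illustrations. A smaller seasonal dip would shrink the loss, since the added mean square goes with the square of the dip. Balance, estimability, the one-third rule and the 12% wider SE follow from Table 1 alone.

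**What to change.** 1. In the within-participant bike-type model, add period (months 1–3, 4–6, 7–9) as a categorical fixed effect. The cost is two residual degrees of freedom (34 to 32) and no change in the variance factor of a bike contrast when data are complete.
2. As a secondary step, pre-specify one sensitivity analysis that adds first-order carry-over, meaning the bike used in the preceding period. Report its bike contrasts beside those of the main model, and state that the wider SE and low power are expected. Do not use a carry-over test to decide which model is reported.
3. Keep the season and weather exploration as a separate objective.

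This changes analysis wording only. It needs no additional participants, visits or data, and the intervention-versus-control comparison and its sample size stay as they are.

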## Conclusion

There is a call for research on the influence of e-bikes and longtail bikes on travel behavior and PA levels, together with increased understanding whether voluntary cycling with different bicycle types could improve health. Attempting to meet this knowledge gap, the present study will address these topics and provide new knowledge relevant for the timely issues of public health and environmental sustainability in a target group of greatest importance, that is, parents of toddlers. If the present study reveals promising results, it should be replicated in larger and more representative samples, enabling a comparison of health effects across the different bicycle types as well. Eventually, inclusion in national public health policies should be considered.

## Abbreviations

DXA: dual-energy X-ray absorptiometry
E-bikes: electric assisted bicycles
GHGs: greenhouse gases
HRQoL: health-related quality of life
METs: metabolic equivalents
MVPA: moderate-to-vigorous physical activity
PA: physical activity
SWA: SenseWear Armband
VO_2_ max: maximum oxygen uptake
